# Effect of Tan Tui combined with kinesio taping on the posture control of patients with PFPS: protocol for a randomized controlled trial

**DOI:** 10.1186/s13063-023-07465-z

**Published:** 2023-08-09

**Keywords:** Patellofemoral pain syndrome, Wushu, Physiotherapy, Randomized controlled trial

## Abstract

**Background:**

Patellofemoral pain syndrome (PFPS) is a chronic disease. Its early symptoms are mild and can be relieved by rest after the pain. If there is no effective rehabilitation, it may develop into patellofemoral arthritis. Physiotherapy and appropriate exercise intervention can improve PFPS and postural control during exercise. Tan Tui (TT) is an effective means to improve postural control. Whether combined kinesio taping (KT) can be used as an effective treatment for PFPS patients’ recovery has not yet been confirmed.

**Methods/design:**

Seventy-two eligible patients with early-stage PFPS will be recruited and randomized into 4 groups: TT + KT group (*n* = 18), TT + KTp group (*n* = 18), KT group (*n* = 18), and CON group (*n* = 18). The TT + KT group was treated with TT combined with KT intervention; the TT + KTp group was treated with TT and KT placebo technical intervention; the KT group was treated with KT intervention alone; the CON group was treated with routine activities. All 4 groups received 30 min, three times a week, for a total of 6 weeks of intervention training. Measurements will be performed at baseline, mid-intervention (4 weeks), and post-intervention (6 weeks) with visual analog scale/score, (VAS), Knee joint Lysholm function score (Lysholm), UniPedal Stance Test (UST), Star Excursion Balance Test ( SEBT), Relative Peak Torque, (RPT), and Knee joint Position PercePtion (KJPP), to check the maintenance of the effect of any intervention.

**Discussion:**

For the first time in this trial, the impact will be evaluated. If the results are the same as expected, they will provide evidence that TT combined with KT sticking intervention can promote the posture control of patients with early PFPS.

**Trial registration:**

Chinese Clinical Trial Registry ChiCTR2100051166. Registered on 15 September 2021.

**Supplementary Information:**

The online version contains supplementary material available at 10.1186/s13063-023-07465-z.

## Background

Patellofemoral pain syndrome (PFPS) refers to a musculoskeletal pain condition caused by patellofemoral joint activity [1]. It is the most common 20.65% of 10–35-year-old sports youth [2, 3]. The main symptoms are anterior knee pain, rubbing noise in the patellofemoral joint, and soft legs, which are further aggravated during physical activity [4], which not only affects the quality of life of patients, but also increases their medical costs [5]. Studies have shown that the early symptoms of PFPS are mild and can be relieved by rest after the pain. If there is no effective rehabilitation, it may develop into patellofemoral arthritis, which will have a long-term impact on the patient’s knee joint health [6]. At present, there is no academic consensus on the occurrence mechanism of PFPS, and most people believe that it is a combination of various factors. It is mainly related to abnormal patella position [7], insufficient gluteal and quadriceps muscle strength [8], abnormal soft tissue tension around the knee joint [9], and patellofemoral joint overload [10].

At present, PFPS interventions are numerous and gradually standardized. It focuses primarily on exercise therapy and has been shown to relieve pain and improve function in the early, middle, and long term [11]. Exercise therapy includes quadriceps exercises [12], hip strength exercises [13], stretching exercises for tissues around the knee joint [14], gait retraining [15], and core muscle exercises [16]. A systematic review of studies discussing the effectiveness of interventions in patients with PFPS reported consistent evidence of pain reduction and functional improvement after several weeks of exercise therapy [17–20].

In addition to exercise therapy, other interventions for PFPS have also achieved significant results, such as kinesio taping (KT). Patellar taping was first proposed by Moconel, which uses taping to pull the patella from the lateral side of the knee to the medial side of the knee to correct the abnormal trajectory of the patella [21]. On this basis, Kinesio proposed the KT technique, which can reduce pain in patients with PFPS [22], improve lower extremity function [23], and increase the knee flexion angle to improve lower extremity postural control [24]. Studies have shown that KT can improve functional abnormalities and enhance quadriceps muscle strength in athletes with PFPS [25], but the results of a systematic review by Barton et al. showed that the use of KT technology could reduce knee pain in the short term, but not in the long term [26]. Therefore, more studies are needed to verify the positive effect of KT on PFPS patients.

Wushu is known as “Southern Boxing and North Legs.” Tan Tui (TT) is a typical example of the Northern School’s proficient leg technique. It is characterized by fast and powerful, left and right symmetry, simple shape, easy to learn, and neat power frame [27]. It is a classic essential skill exercise of Chinese martial arts, known as the “Beginner’s Guide to Playing TT.” After practice, it will have a positive impact on the practitioner’s strength and stability, and other physical qualities. At the same time, it can stabilize the footwork of the lower limbs, and all parts of the body can be developed in a balanced way. When it is static, it is straight and stretched, and when it is moved, it is quick to shoot, which plays a vital role in the control of body posture [28, 29]. At the same time, the ancient Chinese classics of boxing pointed out that the effect of TT is “increasing vigor, steady posture, practicality, and strengthening muscles and bones,” which can significantly improve the lower limb strength and balance ability of practitioners [30]. [name] book on sparring also holds the same point of view [31]. Therefore, TT is an effective means to improve the ability of postural control, but intervention for PFPS patients is rare at present, especially the intervention for Taijiquan PFPS patients.

Currently, there is insufficient evidence to demonstrate the effect of TT or combined with KT on the efficacy and postural control of patients with PFPS. At the same time, the longer the duration of patellofemoral pain, the less successful the treatment will be [32]. Therefore, this paper takes PFPS patients as the intervention object and observes the effect on the curative effect and posture control of PFPS patients through TT or combined KT intervention. Evidence support for prevention.

## Methods/design

### Study purposes

The purpose of this article was to observe the effect of 6-week TT or combined KT on the efficacy and postural control of patients with early PFPS.

### Study design

This is a single-blind randomized controlled trial that recruited 72 eligible early PFPS patients and randomly divided them into 4 groups: TT + KT group, TT + KTp group, KT group, and CON group with a ratio of 1:1. The TT + KT group was intervened with TT combined with intramuscular tape; the TT + KTp group was intervened with TT and intramuscular tape with placebo technical intervention; the KT group was intervened with intramuscular tape alone; the CON group was performed with routine activities. Measurements will be taken at baseline, mid-intervention (4 weeks), and post-intervention (6 weeks) to examine the maintenance of any intervention effects.

### Patient public involvement

The participant flow for this trial is shown in Fig. 1. This protocol follows the Standard Protocol Items: Recommendations for Interventional Trials (SPIRIT) guidelines and meets the SPIRIT checklist (see Additional file 1).

**Fig. 1 Fig1:**
[figure not shown]
Proposed participant flow. TT + KT, kinesio taping + Tan Tui; TT + KTp, placebo kinesio taping + Tan Tui; KT, kinesio taping; CON, control group

### Sample size calculation

The sample size was estimated by the software G*Power 3.1.9 [33]. According to the experimental design of 4 (group) * 3 (time) in this study, repeated measures analysis of variance was used to test the research hypothesis. Under the effect size of 0.25, α of 0.05, and power of 0.8, the sample size requirement was 64 people. After considering the dropout rate of 10%, the overall sample size was calculated to be 71 people. At the same time, combined with the proportionality of the sample size between groups, the final sample size was determined to be 72 people, and each group was about 18 people.

### Setting and recruitment

This study will recruit PFPS patients through WeChat, flyers, and Weibo in the Football Academy of Beijing Sports University, China. The exercise intervention was independently supervised by 3 research assistants at the University, and the other research assistants independently conducted data collection. Due to the impact of the new crown epidemic, this study will officially start recruitment in October 2022.

### Participant eligibility

PFPS patients were recruited for sports-specialized college students at a university in Beijing. Diagnostic criteria [34–36] are as follows: (1) retropatellar or peripatellar pain for ≥ 4 weeks; (2) at least two induced pains when completing functional activities such as hopping on one foot, going up and down stairs, squatting, running, kneeling, and bending knees for a long time; (3) VAS score ≥ 2 when the pain was the most severe in the last week; (4) Lysholm score < 70; (5) at least two of the following signs were positive: tenderness on the patella or patella circumference, crepitus on the patellofemoral joint surface, Fear test, patellofemoral grinding test, knee extension resistance test, single foot squat test. Inclusion criteria were (1) aged 18–30 years; (2) met the diagnostic criteria and had unilateral involvement; (3) did not receive medication or physical therapy; (4) voluntarily signed informed consent. The exclusion criteria were: (1) damage to the tissues around the knee; (2) structural damage to the knee, such as fracture, meniscus tear, or osteoarthritis; (3) allergy to KT; (4) physical activity Medical contraindications (such as cardiovascular disease); and (5) Inability to adhere to the intervention due to personal or other reasons. All subjects voluntarily signed a written informed consent form before the intervention and were given an explanation of the research process by the researchers, strictly following the ethical standards of the Declaration of Helsinki.

### Randomization, allocation, and blinding

In this trial, the assessments and treatments were performed by different therapists. The evaluator was blinded to the subjects’ assignment. All the intervention procedures were performed by the same physiotherapist with experience in the field of sports physical therapy. Both the physiotherapist and the participants were blinded to the purpose of the study. In addition, a different researcher, blinded to the object of the study, carried out the data analysis.

## Intervention

### Intervention plan

#### Kinesio taping

KT function correction technology is a kind of KT technology [37]. The width of the patch is 5 cm, the thickness is 0.05 cm, and it has 70% tension. It is pasted on the skin of the quadriceps muscle, and the natural tension is used to move along the muscle to the tendon, so as to maximize the flexion of the knee joint, the two caudal ends of the muscle tape meet down the tibial tuberosity along both sides of the patella. The calculation of the percentage of tension is based on the length of the KT tile on the paper (0%), and the tape is stretched at maximum tension to measure its length (100%). Therefore, the tension required for KT in this study was 70%, which is 70% of the length between the maximum available tension (100%) of the tape and the base point (0%) [38]. After the taping was completed, the subjects were asked whether there was pain, and they performed half-squatting movements to compare the pain, and the taping was completed if there was no pain.

#### Placebo kinesio taping

The application of the patch was the same as before, but the tension of the patch was 0%, and the patch was only attached to the ankle joint of the subject without any stretching. Both functional correction taping and placebo taping techniques were applied to the subject’s bilateral quadriceps and taped once every 5 days [39, 40].

#### Tan Tui

The selection of the TT exercises is based on the physiological characteristics and physical fitness status of the students in the Taijiquan special class. Through the classification and statistics of the ten-way TT movements 31 compiled by [name]. The proportions of lunges and leg movements were 61% and 17%, respectively, accounting for 78% of the total number of 10-way TT movements. Therefore, this study selects lunges and slings. The sling exercises include three parts: (1) preliminary movements: standing side by side, lunges clasping fists, and lunges punching; (2) TT exercise movements: right Hengquan, right punch, right leg, right lunge punch, left lateral punch, left punch, left leg, left lunge punch; (3) Closing movements: standing side by side (Fig. 2).

**Fig. 2 Fig2:**
[figure not shown]
Tan Tui training movement [31]

In this study, the intervention cycle of bouncing leg exercise lasted for 6 weeks, 3 times a week, 30 min each time. The intervention was divided into two stages of motor learning in the first 1 week and motor improvement in the last 5 weeks. Movement learning stage: The subjects learn new movements in the first week, and can complete a set of movements independently and basically meet the specifications of each movement. The movement improvement stage in the last 5 weeks: the static time of each movement practice is gradually increased from 1 to 5 s, and the interval time is 1 min, 1.5 min, 2 min, 2.5 min, and 3 min, respectively. Each repetition of the exercise can improve its posture control ability.

The requirements of the leg-bounce exercise: the coordination of the strength of the movement and the breathing should be paid attention to during the practice of each movement of the leg-bounce. The method of each movement follows the law of lower limb exertion that starts from the root, follows the middle, and reaches the slightest. The breathing follows the principle of “lifting the breath” and “supporting the breath” [41], and in terms of technical movement standards, the lunge follows the competition rules of martial arts routines ( 2012) [42], the technical movement of the TT requires the support leg to be upright, the spring kick leg to be level with the ground, and the support leg and the pop-up leg to maintain about 90°.

#### CON

Do regular physical activity as usual.

## Outcome assessment test indicators

### Primary outcome

Visual analog scale/score (VAS): VAS was used to evaluate the pain of PFPS patients before and after intervention [43]. On a 10 cm long walking scale, one side has 10 scales, and the two ends are 0 and 10, indicating no pain and the most severe pain, respectively; the other is colored from light to dark, showing different degrees of pain. When using it, turn the scaled side away from the patient, and let the patient mark the corresponding color on the ruler that can represent their pain level, and score [44] according to the position marked by the patient.Knee joint Lysholm function score (Lysholm): Knee joint function is evaluated by the Knee Joint Lysholm Function Score (LKSS), which has been proven to have good reliability and validity [45]. The parameters of the scale (total score 100) mainly include lameness (5 points), twisting (15 points), pain (25 points), support (5 points), instability (25 points), swelling (10 points), Going up and down stairs (10 points), squatting and standing up (5 points), basically covering all symptoms of patients with patellofemoral joint disease. The size of the score is positively correlated with the functional status of the knee joint of patients, and the higher the score, the better the joint function [46].Static balance: The static balance ability of the dominant side of the subjects was assessed by the UniPedal Stance Test (UST) with eyes closed. UST has been shown to have high scoring reliability (ICC = 0.998) [47], and its test refers to the method of previous literature [48]. Before the formal test, the subject’s heart rate should reach a quiet level, and perform 4 test exercises. At the beginning of the formal test, stand on one foot with eyes closed according to the test requirements, and stop timing when the supporting leg is displaced, eyes are opened, or the non-supporting leg touches the ground. Each subject repeated the test 3 times with 20 s rest intervals, and the average of the 3 test scores was the final test score of the subjects.Dynamic balance: The Star Excursion Balance Test (SEBT) was used to evaluate the dynamic balance ability of the dominant side of the subjects. SEBT is a comprehensive quality, including strength, flexibility, and coordination quality, which is widely used to evaluate the dynamic stability of lower limbs [49], and its test method refers to previous studies [50]. Before the formal test, to reduce the test error caused by the learning effect, the subjects performed the test practice 4 times. In the formal test, the subject (left or right foot) is required to stand on one foot, with both hands on the hip, and the non-supporting leg is extended as far as possible in front of the supporting leg, the back-inward direction, and the back-outward direction, respectively, and the non-supporting leg is retracted and close to the supporting leg, then start the next reach. The subject’s supporting leg moved, the non-supporting leg touched the ground, or the non-supporting leg reached quickly and far rather than sustained force during the test was considered a failure. The subject’s measurement in each direction is 3 times, with a 20-s rest between each time. The average of the 3 test data is the subject’s final score in that direction, and the total comprehensive value is the average of the 3 directions. SEBT has been shown to have good internal reliability (ICC = 0.86–0.94)52 [51] and test–retest reliability (ICC = 0.89–0.93) [52].

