### Statistical analysis

Statistical analysis will be performed by the Statistical Package for Social Sciences (The Statistical Package for Social Sciences, SPSS 23, SPSS Inc., Chicago, IL, USA). ShaPiro Wilk will be used to test whether the variables of the two-way multivariate analysis of variance conform to the normal distribution. One-way multivariate analysis of variance will be used to compare the baseline age, height, and weight data of participants, to explore whether there is homogeneity between groups. Descriptive statistical analysis will be conducted in the form of mean ± standard deviation. Two-way multivariate analysis of variance will be used to perform inference analysis on the effect of the intervention group (e.g., TT + KT, KTp + TT, KT, CON) and time (e.g., pre-intervention, during intervention, post-intervention), in order to examine group effect and time effect and The interaction effect of time and group. Pairwise comparisons of variables with significant effects in ANOVA will be conducted by post hoc analysis and Bonferroni correction to find time effects by group and group effects by time. According to Cohen’s method, the effect size will be divided into large (0.8), medium (0.50–0.79), and small (0.20–0.49) to judge the significance of the intervention effect [55]. *P* < 0.05 means there is a significant difference, and *P* < 0.01 means the difference is extremely significant.

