## Discussion

The primary purpose of this study was to observe the effect of TT or combined with KT on the curative effect and postural control of patients with PFPS. The related parameters of curative effect were pain and knee function; the associated parameters of postural control were static balance, dynamic balance, knee muscle Force, and knee proprioception. The best method to improve the curative effect and postural control ability of PFPS patients has not yet been obtained [56]. The intervention in this paper will provide a new method for the rehabilitation of PFPS patients.

Studies generally believe that intervention in the knee joint of patients with PFPS can significantly improve patellofemoral pain and knee function. Some studies have performed knee strength training alone or combined with hip strength training in patients with PFPS and found that both interventions can achieve the effect of reducing pain and improving function, but the effect of the hip joint combined with knee strength training group is better than that of the simple group. Knee Strength Training Group [13, 57]. Valenza et al. randomly divided 84 patients with PFPS into a soft tissue stretching group, a transcutaneous electrical stimulation group, and a control group, and compared the immediate effects of the two interventions on the range of motion and pain of the knee joint. The results showed that both groups improved the range of motion of the joint, and reduced pain, but the soft-tissue stretch group had better treatment effects [14]. The characteristics of the TT exercise are mainly the flexion and extension of the hip and knee joints. When the joint is extended, it is supported by one leg. When the other leg pops out and performs a short-term isotonic contraction, it can effectively stimulate the muscles around the hip and knee joints. At the same time, it can quickly stretch the soft tissues around the knee joint at the moment of popping up; when the joint is flexed, it is performed as a lunge action, and the quadriceps of the front leg performs isotonic contraction to enhance its muscle strength. It can be seen that the TT can not only improve the strength of the hip and knee joint, but also enhance the flexibility of the soft tissue around the knee joint.

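### Four unranked primary outcomes share one 0.05 threshold with no rule across them: if any one positive counts, familywise error is about 10% to 18.5%, not 5%

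*Protocol article*

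**What the plan says.** In the protocol article, the section Primary outcome describes four measures in turn and puts none above the others:

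- VAS pain: "VAS was used to evaluate the pain of PFPS patients before and after intervention".
- The Lysholm knee function score, out of 100, of which pain contributes 25 points.
- Static balance: "The static balance ability of the dominant side of the subjects was assessed by the UniPedal Stance Test (UST) with eyes closed".
- Dynamic balance: "The Star Excursion Balance Test (SEBT) was used to evaluate the dynamic balance ability of the dominant side of the subjects". This yields three direction scores and a composite that averages them.

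The section Statistical analysis plans a two-way multivariate analysis of variance for group, time and their interaction. It does not say which outcomes enter it jointly, or whether a joint result must be significant before single outcomes are read. The decision rule is P "< 0.05 means there is a significant difference". The only multiplicity control is: "Pairwise comparisons of variables with significant effects in ANOVA will be conducted by post hoc analysis and Bonferroni correction".

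The section Sample size calculation sizes the trial for one repeated measures analysis of variance (4 groups by 3 times) with effect size 0.25, α 0.05 and power 0.8. This gives 64 people, 71 after 10% dropout, and 72 for equal groups.

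No section gives a testing order, a split of alpha, or a rule that all four primaries must succeed.

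**The concern.** Bonferroni as written acts inside one variable, among pairs of groups or time points, and only after that variable has shown a significant effect. Nothing acts across the four primaries. A reader following the text can declare a positive primary result from whichever of the four falls below 0.05. The stated 5% then describes each test, not the set on which the trial's conclusion rests. The sample size has the same limit: its 80% power belongs to one test at 0.05, although four outcomes carry primary status.

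**Working it through.** **Inputs.** From the article: four primary outcomes; threshold 0.05; k = 4 groups; m = 3 times; f = 0.25; power 0.80; N = 64; dropout 10%. Assumptions, because the article does not give them: the correlation ρ between repeated measures, the sphericity factor ε, and the correlation r between outcomes.

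**1. Reproducing the plan's 64.** Power comes from the noncentral F distribution, with N in multiples of 4.

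- Group-by-time test: λ = f²·N·m·ε/(1 − ρ), with (m − 1)(k − 1)ε and (N − k)(m − 1)ε degrees of freedom.
  - ρ = 0.2, ε = 1, N = 64: λ = 0.0625 × 64 × 3/0.8 = 15; df 6 and 120; power 0.820.
  - ρ = 0.5, ε = 0.5, N = 64: λ = 0.0625 × 64 × 3 × 0.5/0.5 = 12; df 3 and 60; power 0.813.
- Between-group test: λ = f²·N·m/(1 + (m − 1)ρ). With ρ = 0, λ = 12; df 3 and 60; power 0.813.

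Each of these three settings gives 64 as the required N, so the figure reproduces. It depends on the unstated settings: ρ = 0.5 with ε = 1 would give 40 for the interaction and 124 between groups. For dropout, 64 × 1.1 = 70.4, rounded up to 71, and 64/0.9 = 71.1, rounded up to 72. The final 72 fits either.

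**2. Error across four primaries tested separately.** If independent, 1 − 0.95⁴ = 1 − 0.8145 = 18.5%. With a common correlation r, the group-by-time test was simulated with 16 per group, no true effect, and 20,000 runs per row:

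| r | at least one of four below 0.05 |
|---|---|
| 0 | 18.4% |
| 0.3 | 17.9% |
| 0.5 | 16.4% |
| 0.7 | 13.8% |
| 0.9 | 10.0% |

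**3. If a joint multivariate test had to be significant first.** The same simulation was run with a Pillai test on all four outcomes as the first step. With no outcome affected, the error is 1.8% to 3.8% over the same range of r. With one outcome truly affected (8,000 runs), the chance of a false positive among the other three is 8.9% to 14.3%. Without the first step it is 8.9% to 14.4%, so once one effect is real the joint test protects almost nothing.

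**4. Effect of control across the four.** At 0.05/4 = 0.0125 each, the familywise error is 1 − 0.9875⁴ = 4.9% if independent and at most 5% otherwise. Under the three settings that reproduce 64:

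- Power per outcome at 0.0125 is 0.626 to 0.642 with 64 analysed and 0.703 to 0.721 with 72.
- Restoring 80% at 0.0125 needs 84 to 88 analysed. Dividing by 0.9 gives 93.3 to 97.8, so 94 to 98 recruited, or 96 to 100 in equal groups.

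**The case against.** **The multivariate analysis may already be a joint test.** On its face, a multivariate analysis of variance tests outcomes together, so separate testing at 0.05 is not certain. This stands as a limit on the 18.5%. It does not remove the problem: the text states no such first step, it follows up variables that are significant in a univariate-sounding analysis, the sample size section names a repeated measures analysis, and step 3 shows that the protection fails once one outcome responds.

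**The outcomes are correlated.** This is fair. Pain is a quarter of the Lysholm score, so VAS and Lysholm share content, and 18.5% is the independent case. Even at r = 0.9 the rate is twice the nominal 5%.

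**A statistical analysis plan may settle it.** Which outcomes enter jointly can be left to that document. But this article itself fixes four primaries, one threshold and the narrow scope of Bonferroni, and the point rests on those.

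**Stronger readings that the article does not support.** A reader might count the group and interaction tests for each primary as eight chances and quote a much larger error. That needs eight independent tests and a rule that either effect counts as success, and neither is stated. A reader might also infer that pain and function are misplaced as primaries because the title speaks of posture control. Study purposes and Discussion both set a dual aim. Discussion assigns pain and knee function to curative effect, and for the other aim says that "the associated parameters of postural control were static balance, dynamic balance, knee muscle Force, and knee proprioception". The four primaries serve those two aims, so this is not a contradiction.

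**Conclusion.** The point holds conditionally. If the four primaries are tested separately and any one positive counts as success, the familywise error is about 10% to 18.5% for outcome correlations of 0.9 down to 0, which is two to nearly four times the 5% that the threshold suggests. The correlations are assumed, not taken from the article. A rule requiring all four to succeed would not inflate the error, but none is stated. If the multivariate test were used as a joint first step, error would be held only when nothing is affected, with about 9% to 14% among the remaining three once one outcome is. The choice of these four outcomes is not itself at fault; what is missing is a rule across them.

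**What to change.** **Change.** Keep VAS, Lysholm, UST and SEBT as primaries, since together they cover both stated aims. Name the SEBT composite as the single SEBT measure. Apply Holm to the four group-by-time tests, with the smallest p-value against 0.0125 and then 0.05/3 = 0.0167, 0.025 and 0.05. State that a primary claim is made only for outcomes that pass. The Bonferroni correction for pairs within an outcome can stay as follow-up.

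**Alternative.** The sponsor may name one primary outcome of its own choice, which keeps 5% and the planned 72, provided this is done before outcome data are seen. Trial status planned testing from the end of November 2022 and the article appeared in August 2023, so data may already exist. If they have been seen, Holm is the safer course because it selects nothing.

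**Cost.** Protocol, analysis plan and registry wording; no new data or participants. The statistical price is the power in step 4. Because Holm rejects everything that a flat 0.0125 would, those figures are a floor for each outcome. Sample size calculation should say that 80% power applies to a single outcome at 0.05, and should state the repeated-measures correlation and sphericity settings behind 64. Restoring 80% at 0.0125 would need 96 to 100 recruited; that is an option, not a condition of this fix.
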